### Trial procedures

#### Screening

The purpose of the screening is to verify the eligibility of potential participants selected from the Department of Outpatient. The recruitment of participants will be done in the Department of Endocrinology of Shanghai East Hospital, Shanghai, China. Every potential participant will be informed the detailed information of the objectives of the study, the participated risks and the expected benefits. When the concert form has been signed, participants will be asked to fill a standardized questionnaire about medical history and to undergo a 75 g OGTT, insulin release test, liver and kidney function test (blood draw after 8 h overnight fasting and 30 min and 2 h after glucose load).

#### First visit

Before the first visit, a physician examines all the results of the screening to verify whether the subject meets the inclusion criteria. In the first visit (within 1 week of the screening), if a person is qualified for participation in the study (fasting glucose <6.1 mmol/L, and 2-h post glucose load ≥7.8 and <11.1 mmol/L, with no other chronic diseases), he or she will be invited to the clinical laboratory of Department of Endocrinology, Shanghai East Hospital for height, weight, waist circumference and blood pressure measurement, as well as instructions for fecal sample. Then they will be randomized and assigned in double-blind to receive either probiotics or placebo for 8 weeks. We emphasize the importance of their participation in study and instruct them to take medicine on time during the intervention.

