#### Follow-up visits

The purpose of follow-up visits is to monitor the compliance and to discover the adverse events. After the first visit, a researcher will contact participants every month to check their medication. The participants will have follow-up visits to the clinical laboratory every 2 months. Their height, weight, waist circumference, hip circumference, blood pressure, heart rate and newly combined medication will be checked at those time points. In addition, at months 6, 12, 18, 24, participants will undergo a 75 g OGTT to evaluate the glycemic status (blood draw after 8 h overnight fasting and 30 min and 2 h after glucose load) and take blood samples and fecal samples (Table 1).

**Table 1 Tab1:** Visit study and efficacy variables for Probiotics Prevention Diabetes Programme (PPDP)

Visit number	1	2	3	4	5	6	7	8	9	10	11	12	13
Study month	0	2 m	4 m	6 m	8 m	10 m	12 m	14 m	16 m	18 m	20 m	22 m	24 m
Newly diagnosed diabetes(*n*)	×			×			×			×			×
OGTT + IRT(0 min,30 min,2 h)^a^	×			×			×			×			×
Total cholesterol	×			×			×			×			×
Triglyceride	×			×			×			×			×
High-density lipoprotein	×			×			×			×			×
Low-density lipoprotein	×			×			×			×			×
Body weight	×	×	×	×	×	×	×	×	×	×	×	×	×
Systolic blood pressure	×	×	×	×	×	×	×	×	×	×	×	×	×
Diastolic blood pressure	×	×	×	×	×	×	×	×	×	×	×	×	×
Waist circumference	×	×	×	×	×	×	×	×	×	×	×	×	×
Hip circumference	×			×			×			×			×
Abundance of bacteria	×			×			×			×			×
LPS	×			×			×			×			×
GLP-1	×			×			×			×			×

^a^OGTT, oral glucose tolerance test; IRT, insulin release test; LPS, lipopolysaccharides

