#### Stool samples collection

The stool samples will be collected at the first visit and at months 6, 12, 18, 24. Detailed stool sample collection and transportation instructions will be given by a study researcher. We will provide to subjects the materials for sample collection and transportation from home to hospital which including: 1 cool box, 1 sterile dressing room, 1 sterile EP tubes, 1 pair of sterile tweezer, 1 pair of plastic gloves and a plastic bag. The participants are advised to sample approximately 5 g of feces by tweezer attached to the sterile EP tubes. Then the sterile EP tubes are stored in a plastic bag in the cool box. After samples are collected, the subjects will immediately deliver the samples to the clinical laboratory in 1 h.

The stool samples will be frozen at −80 °C after collected and the DNA extraction will be performed using the E.Z.N.A.^®^ Stool DNA Kit (Omega Bio-tek, Norcross, GA, U.S.) according to manufacturer’s protocols. Fecal bacteria composition will be determined using 16S rRNA based methods and illumina MiSeq sequencing.

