### Statistical methods

All analyses of end points are based on the intention-to-treat (ITT) principle. The results of the trial are reported as comparative summary statistics (difference in response rate or means) with 95 % confidence intervals. All statistical tests use a 5 % with two-sided significance level. Two-sided *t*-tests and chi-square tests are used to analyze the differences between the groups at baseline and during follow-up. For the primary outcome, survival curves are used to calculate the cumulative incidence of diabetes. The difference between the groups in the incidence of diabetes is tested by means of the two-sided log-rank test. For the secondary outcomes (the difference of the changes of blood glucose, lipid profile and insulin sensitivity, body weight, waist circumference, abundance of bacteria, levels of LPS and GLP-1 between the two groups), a mixed models are used on data collected at 6,12,18 and 24 months. An interaction between treatment group and time is fitted to allow estimation of treatment effects at each time point. The model adjusts for baseline variable and minimization factors. Linear Pearson’s correlation, partial correlation, and logistic regression analysis are used for analyzing relationships.

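### The protocol's sections do not agree on when the baseline stool is taken, so it can fall after randomisation and possibly after the first tablets

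*Protocol article*

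**What the plan says.** All references are to the protocol article.

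- **Screening** has participants complete a questionnaire and "to undergo a 75 g OGTT, insulin release test, liver and kidney function test". It mentions no stool kit and no stool instructions.
- **First visit**, within one week of screening, lists body measurements and blood pressure, "as well as instructions for fecal sample. Then they will be randomized and assigned in double-blind to receive either probiotics or placebo". Staff also "instruct them to take medicine on time during the intervention". The section gives neither the day the tablets are handed over nor the day of the first dose.
- **Stool samples collection** states: "The stool samples will be collected at the first visit and at months 6, 12, 18, 24". It also says that participants receive "materials for sample collection and transportation from home to hospital", and that after collection "the subjects will immediately deliver the samples to the clinical laboratory in 1 h".
- **Table 1**, under Follow-up visits, marks "Abundance of bacteria" at visit 1 (month 0) and at months 6, 12, 18 and 24.
- **Secondary outcomes**, item (v), is the change in gut bacterial abundance.
- **Statistical methods** plans mixed models for the secondary outcomes on data from months 6 to 24, and adds: "The model adjusts for baseline variable and minimization factors".

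**The concern.** A baseline for a microbiota outcome must describe the participant before exposure to the study product. Here the product is itself live bacteria, and the readout is 16S rRNA sequencing of stool. A stool passed after the first doses could carry the product's organisms, or an early shift they cause, in the active arm only.

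The baseline would then differ between arms because of treatment. A change score would subtract part of the effect it is meant to show. A model adjusted for that baseline would condition on a variable measured after randomisation and already affected by it.

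At stake is secondary outcome (v). The Discussion also expects the metabolic benefit to come about through a change in the gut microbiota, so this outcome carries the trial's mechanistic argument.

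**Working it through.** The plan gives no figure to reproduce. The check is whether the stated steps can all be carried out, and what follows if they cannot.

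**Step 1: the order of events.**

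| Question | What the article states | Where |
|---|---|---|
| When are stool instructions first given? | At visit 1, directly before randomisation | First visit; nothing in Screening |
| Where is the sample taken? | At home, with a supplied kit, then brought in within 1 h | Stool samples collection |
| Which visit does it belong to? | First visit, month 0 | Stool samples collection; Table 1 |
| When does randomisation occur? | At visit 1, after the instructions | First visit |
| Must the stool precede randomisation or first dose? | Not stated | No section |
| When is the first dose? | Not stated | No section |

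A participant who first hears how to sample at visit 1 cannot arrive at visit 1 with a sample taken at home by those instructions. One statement has to give way: the instructions come earlier than stated, the baseline sample is not a home sample, or it arrives after the randomisation step. The article does not say which.

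**Step 2: can the sample follow the first dose?** It can, because nothing prevents it. After visit 1 the next visit in Table 1 is month 2, and no separate dispensing visit is described. Tablets handed over at visit 1 are therefore a plausible reading, but remain an inference. Trial status says that baseline measurement and the intervention both began in October 2014, which does not settle the order within a participant.

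**Step 3: direction of the bias.** Let D be the true on-treatment shift in abundance (active minus placebo), f the fraction of active-arm baseline stools taken after dosing began, s the share of D already present in those stools, and b the coefficient of baseline in the mixed model.

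- Treatment-induced difference between arms at baseline: f × s × D.
- Raw change score: D − f × s × D = D × (1 − f × s).
- Baseline-adjusted model, to a first approximation: D × (1 − b × f × s).

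With s and b between 0 and 1, both estimates lie between zero and D, and the adjusted one loses less. If f = 0, nothing is lost. The documents give no value for f, s or b, so the formulas fix the direction but not the size.

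**The case against.** **The article places the sample at the first visit.** This is the strongest point. Stool samples collection says so and Table 1 agrees. A reader might infer that the protocol sets the baseline stool up to be collected after the visit, with tablets already in hand. The documents do not support that: collection after the visit and tablet hand-over at the visit are both inferences. What stands is narrower: the sections conflict, and the conflict leaves room for a post-dose baseline.

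**An article condenses the full protocol.** The logistics of kits may well be set out elsewhere. But this is not mere silence. The article states both the order of steps and the place of collection, and the two do not fit.

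**Baseline blood tests.** A reader might extend the point to lipids, LPS and GLP-1, which Table 1 marks at month 0 but neither Screening nor First visit lists. That is only a listing gap. Hip circumference is also marked at month 0 and missing from First visit, so the narrative is not exhaustive. Blood samples describes fasting morning venous draws, home collection plays no part, and nothing suggests they follow dosing.

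**Size.** A reader might enter f = 0.5 and s = 0.5 to 1 and obtain a loss of 0.5 × 0.5 = 25% to 0.5 × 1 = 50%. Those inputs have no source in the documents, and the result applies to a raw change score. In the planned baseline-adjusted model it would be multiplied by b.

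**Limited consequence.** This stands. Only one secondary outcome is touched, the expected bias is toward zero, and the randomised comparison of follow-up stools without a baseline remains valid.

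**Conclusion.** The point holds as an inconsistency that needs reconciling. Screening, First visit, Table 1 and Stool samples collection cannot all be followed for the month-0 stool, and no section ties that stool to randomisation or to the first dose. As written, the baseline for secondary outcome (v) can be post-randomisation and possibly post-dose.

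If that happens, the change or the baseline-adjusted effect tends toward zero. This rests on two assumptions: that the early shift has the same direction as the later one without exceeding it, and that the baseline coefficient lies between 0 and 1. The amount cannot be derived from the documents. A stool taken after randomisation but before any study product would not be contaminated in this way. The primary diabetes outcome and the baseline blood tests are unaffected.

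**What to change.** Reconcile Screening, First visit, Table 1 and Stool samples collection so that:

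- the stool kit and instructions are given at screening, or when an eligible person is invited to the first visit;
- the month-0 stool is received before randomisation.

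For participants already enrolled, record the date of the first stool relative to the start of study product. In the microbiota analysis, do not use stools taken after that start as baseline values, and apply this rule to both arms before the allocation is revealed.

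The cost is small. The first visit falls within one week of screening, so the kit goes out at most about a week earlier and no visit is added. Some kits will go to people who fail screening, and a few baseline values may be lost. Trial status has recruitment continuing until October 2015, so participants still to be enrolled at the time of the article could benefit.

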#### Follow-up visits

The purpose of follow-up visits is to monitor the compliance and to discover the adverse events. After the first visit, a researcher will contact participants every month to check their medication. The participants will have follow-up visits to the clinical laboratory every 2 months. Their height, weight, waist circumference, hip circumference, blood pressure, heart rate and newly combined medication will be checked at those time points. In addition, at months 6, 12, 18, 24, participants will undergo a 75 g OGTT to evaluate the glycemic status (blood draw after 8 h overnight fasting and 30 min and 2 h after glucose load) and take blood samples and fecal samples (Table 1).

**Table 1 Tab1:** Visit study and efficacy variables for Probiotics Prevention Diabetes Programme (PPDP)

Visit number	1	2	3	4	5	6	7	8	9	10	11	12	13
Study month	0	2 m	4 m	6 m	8 m	10 m	12 m	14 m	16 m	18 m	20 m	22 m	24 m
Newly diagnosed diabetes(*n*)	×			×			×			×			×
OGTT + IRT(0 min,30 min,2 h)^a^	×			×			×			×			×
Total cholesterol	×			×			×			×			×
Triglyceride	×			×			×			×			×
High-density lipoprotein	×			×			×			×			×
Low-density lipoprotein	×			×			×			×			×
Body weight	×	×	×	×	×	×	×	×	×	×	×	×	×
Systolic blood pressure	×	×	×	×	×	×	×	×	×	×	×	×	×
Diastolic blood pressure	×	×	×	×	×	×	×	×	×	×	×	×	×
Waist circumference	×	×	×	×	×	×	×	×	×	×	×	×	×
Hip circumference	×			×			×			×			×
Abundance of bacteria	×			×			×			×			×
LPS	×			×			×			×			×
GLP-1	×			×			×			×			×

^a^OGTT, oral glucose tolerance test; IRT, insulin release test; LPS, lipopolysaccharides

### Methods of measurements

#### Physical examinations

Height and weight will be measured with light clothes and without shoes. Waist circumference will be measured at the level midway between the lower rib margin and the iliac crest. Hip circumference will be measured at the widest part of your buttocks. Body mass index (BMI) is calculated as weight (kg) divided by the square of height (m). Blood pressure will be measured twice after each subject had been seated for 10 min using a mercury electric sphygmomanometer. The average will be used for analysis.

#### Blood samples

OGTT will be performed after overnight fasting, 30 min and 2 h after the intake of 75 g glucose for the assessment of serum insulin and glucose levels. The blood samples were frozen at −80 °C until assayed. Venous blood samples will be collected after fasting over 8 h at 7 ~ 8 a.m. for the measurement of triglyceride and total cholesterol, high-density lipoprotein and low-density lipoprotein, and LPS and GLP-1 levels.

#### Stool samples collection

The stool samples will be collected at the first visit and at months 6, 12, 18, 24. Detailed stool sample collection and transportation instructions will be given by a study researcher. We will provide to subjects the materials for sample collection and transportation from home to hospital which including: 1 cool box, 1 sterile dressing room, 1 sterile EP tubes, 1 pair of sterile tweezer, 1 pair of plastic gloves and a plastic bag. The participants are advised to sample approximately 5 g of feces by tweezer attached to the sterile EP tubes. Then the sterile EP tubes are stored in a plastic bag in the cool box. After samples are collected, the subjects will immediately deliver the samples to the clinical laboratory in 1 h.

The stool samples will be frozen at −80 °C after collected and the DNA extraction will be performed using the E.Z.N.A.^®^ Stool DNA Kit (Omega Bio-tek, Norcross, GA, U.S.) according to manufacturer’s protocols. Fecal bacteria composition will be determined using 16S rRNA based methods and illumina MiSeq sequencing.

### Treatment compliance

The administration of study drugs will be recorded. Compliance will be discussed at each study visit and assessed based on returned tablet counts. Patients will be asked to return all unused study products including empty packages to the clinic at each visit.

### Sample size calculations

We will aim to recruit 100 subjects in each arm of the trial. Assuming a rate of 35 % developing diabetes in placebo group in China [20, 21], a type I error of 0.05 with two-sided, we have 80 % power to detect a 14 % difference in probiotics group at 2 year follow-up (accounting for our primary outcomes).

Considering a dropout rate of 10 %, the sample size for enrolled patients will rise up to 220 for all patients.

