### Randomization

Participants are individually randomized to placebo or probiotics groups in a 1:1 allocation. Random number are generated by excel and overseen by an independent statistician. Research staff and participants remain blind to the allocated treatment group.

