## Discussion

IGT is associated with progressing to diabetes and risk of cardiovascular diseases. Epidemiological studies showed that 25 % of patients with IGT progress to type 2 diabetes in 5 years [2] and the rate reach to 41 % in China [20]. An unhealthy diet and the alterations in gut microbiota play an important role in this process. Although the diet control is helpful to the prevention and treatment of diabetes, it is difficult for the individual to insist on. Recent studies showed that reshaping the gut microbiome can improve the energy metabolism [16–19, 22], which provide a new insight on preventing the occurrence of type 2 diabetes. Therefore, we present a design of a randomized double-blinded, placebo-controlled trial to investigate the efficacy and safety of probiotics intervention in preventing conversion of IGT to type 2 diabetes in China. To the best of our knowledge, this is the first study, in a relative larger sample and in a longer period, to evaluate the efficacy of probiotics administration on glucose metabolism in IGT subjects.

This trial has been designed to address the limitations of previous studies of the effects of probiotics administration on the outcomes of metabolic diseases. The duration of intervention and the sample size will allow us to explore the effects of probiotics intervention on metabolic diseases. We expect that the overall incidence of diabetes will be significantly reduced in probiotics group than placebo group, which suggest that type 2 diabetes can be prevented by oral administration probiotics for subjects at high risk for the disease. We also anticipate that probiotics intervention will improve insulin sensitivity, lipid profile, and inflammatory state by changing the gut microbiota composition.

This trial using oral administration of probiotics offers a new approach for both diabetes and metabolic diseases prevention. If the result of the research shown to be effective, it will open a new strategy for diabetes prevention.

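### The 35% two-year placebo rate behind the sample size is not reconciled with the 41% Chinese rate in the Discussion, and the stated 80% power does not hold even at 35%

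*Protocol article*

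**What the plan says.** Protocol article, Sample size calculations:

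- Placebo rate: "Assuming a rate of 35 % developing diabetes in placebo group in China [20, 21", that is, references 20 and 21 together.
- Target: "we have 80 % power to detect a 14 % difference in probiotics group at 2 year follow-up".
- Error rate: "a type I error of 0.05 with two-sided".
- Size: "We will aim to recruit 100 subjects in each arm of the trial"; then "Considering a dropout rate of 10 %, the sample size for enrolled patients will rise up to 220 for all patients".

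The Randomization section fixes 1:1 allocation. Statistical methods names a two-sided log-rank test for the incidence of diabetes.

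The Discussion says that 25% of people with impaired glucose tolerance "progress to type 2 diabetes in 5 years [2] and the rate reach to 41 % in China [20". Reference 20 is therefore cited for both the 35% and the 41%. Reference 21 is cited only for the 35%. The article does not explain how the two figures relate.

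**The concern.** The two figures describe the same event, in the same condition and country, and share a citation. Yet the planning rate puts 35% conversion into two years, where the background rate puts 41% into what reads as five. If the background rate is the better guide, the placebo arm will yield roughly half the planned events. The primary test is a log-rank test, whose power depends on the number of events, so a null result could then say little about whether the product works. This matters more because the margin is already missing: the quoted power is not reached at the article's own 35%.

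**Working it through.** **Inputs.** From Sample size calculations: placebo 35% at two years, a 14-point difference read as absolute (35% versus 21%), 100 per arm, two-sided 0.05. From the Discussion: 41%, taken as five-year. Derived: risk ratio 0.21/0.35 = 0.60; hazard ratio ln(0.79)/ln(0.65) = 0.547.

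**Step 1: the plan's own figure.** For two proportions with pooled variance under the null,

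power = Φ{[d√n − 1.96√(2p̄q̄)] / √(p₁q₁ + p₂q₂)}.

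With d = 0.14, n = 100, p̄ = 0.28: [1.400 − 1.96 × 0.635] / 0.627 = 0.248, so power = 60%.

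- Unpooled variance gives 61% and the arcsine method 60%.
- Log-rank: expected events are 100 × (0.35 + 0.21) = 56. Power = Φ{(√56/2) × |ln 0.547| − 1.96} = Φ(0.296) = 62%.
- Analysing all 220 enrolled (110 per arm) gives 64%. A one-sided test at 100 per arm gives 71–73%.
- 80% power needs 161 per arm by the pooled formula.
- Other readings of the 14% do not give 80% either: 35% versus 14% gives 94%, a 14% relative reduction 11%, and 35% versus 49% 52%.

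The stated 80% is not reproduced.

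**Step 2: put the two rates on one time scale.**

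- 41% at five years, constant hazard: 1 − (1 − 0.41)^(2/5) = 19.0% at two years. Linear: 0.41 × 2/5 = 16.4%.
- 35% at two years, constant hazard: 1 − 0.65^(5/2) = 65.9% at five years.
- For both to hold in one cohort, only (0.41 − 0.35)/0.65 = 9% of those still free of diabetes at year 2 could convert in years 3 to 5. The hazard would have to fall from −ln(0.65)/2 = 0.215 to ln(0.65/0.59)/3 = 0.032 per year, about 6.7-fold.

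**Step 3: power at the lower rate, 100 per arm.** The answer depends on which effect measure is held fixed.

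- Risk ratio 0.60: 19.0% versus 11.4%, 30.4 events. [0.761 − 0.996] / 0.505 = −0.465, so power is 32% (33% by log-rank). 80% needs 349 per arm.
- Hazard ratio 0.547: 19.0% versus 10.9%, 29.9 events. Power is 36% by proportions; by log-rank, Φ{(√29.9/2) × 0.603 − 1.96} = 38%. 80% needs 302 per arm.
- Absolute 14 points: 19.0% versus 5.0%, a relative reduction of 0.14/0.19 = 74%. Power is 87%.

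**Step 4: power over the range of placebo rates** (two proportions, 100 per arm).

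| Two-year placebo rate | Risk ratio 0.60 kept | Absolute 14 points kept |
|---|---|---|
| 16.4% | 28% (vs 9.8%) | 93% (vs 2.4%) |
| 19.0% | 32% (vs 11.4%) | 87% (vs 5.0%) |
| 25% | 42% (vs 15%) | not computed |
| 30% | 51% (vs 18%) | not computed |
| 35% | 60% (vs 21%) | 60% (vs 21%) |

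Keeping the hazard ratio instead gives 32–33% at 16.4% and 36–38% at 19.0%.

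**The case against.** A reader might infer that the article contradicts itself, with one source giving two incompatible rates. The documents do not carry that. The 35% also rests on reference 21, which may report a faster-converting cohort. The five-year horizon is attached in words to the 25% figure and reaches the 41% only through the sentence's grammar. The conversion also assumes a constant hazard and comparable cohorts and ascertainment. The Abstract describes participants whose impaired glucose tolerance had persisted, and the follow-up schedule tests glucose tolerance every six months, which may find more and earlier cases than sparser testing. All of this stands. None of it is offered in the article as the reason for 35%, and the First visit section describes only a single qualifying glucose tolerance result. The 19% is therefore a scenario built from the article's figures, not a rate the article states.

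A reader might also infer that the trial simply has one-third power. That needs a further assumption. The article plans an absolute difference, and the 40% relative reduction is derived from it. Holding 14 points fixed gives 87% at a 19% placebo rate. This is correct arithmetic, but a 74% relative reduction is a different hypothesis from the 40% implied by the plan, so keeping the relative effect is the more sensible scenario. It still has to be named as a choice.

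Finally, a reader might infer that the lower rate alone takes power from 80% to about a third. It does not: the starting point is about 60%.

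**Conclusion.** The point holds as an unreconciled planning assumption together with a wrong power statement.

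- Without any assumption about the true event rate, and reading the 14% as absolute, 80% should be about 60% (62% by log-rank).
- Conditional on 41% being a five-year rate, a roughly constant hazard, a comparable cohort, and the relative effect being preserved, power drops further to about 32–38%, with about 30 events instead of 56.

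The second statement is only as firm as those conditions, and reference 21 could weaken it. The first does not depend on them.

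**What to change.** In Sample size calculations:

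1. State the two-year placebo rate that each of references 20 and 21 supports, with its follow-up period and how it was converted, and say why 35% was chosen beside the Discussion's 41%. State the time horizon of the 41% explicitly.
2. Correct the stated 80% power for 100 per arm at 35% versus 21%.
3. Report power for 100 per arm over two-year placebo rates of about 16% to 35%, naming the effect measure held fixed (risk ratio, hazard ratio or absolute difference).

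The cost is wording, a short table, and a less favourable stated power. These changes make the claim accurate; they do not restore power. If a rate near 19% proves credible, the sponsor will face the 302–349 per arm shown above, and should then say plainly what 100 per arm can detect. A blinded tabulation of pooled events at month 12, when glucose tolerance tests are already scheduled, would be a useful extra but is optional and not part of this fix.

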**Methods/Design:**

A 24-month randomized intervention is conducted from January 2014 to December 2016. The target sample size for intervention is 200 middle-aged men and women aged 30–65 year-old with impaired glucose tolerance. Participants with persistent impaired glucose tolerance were assigned to group A (tablet A) and B (tablet B) in sequential order. The participants and investigators were blinded to the assignment. The primary outcome is development of diabetes. The secondary outcome measures include body composition, biochemical variables and the safety of the probiotics.

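### The stated 80% power for a 14-point difference with 100 per arm is wrong: the protocol's own inputs give about 60%

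*Protocol article*

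**What the plan says.** The protocol article, under Sample size calculations, gives a complete set of inputs and a result:

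- Size: "We will aim to recruit 100 subjects in each arm of the trial".
- Control rate: "Assuming a rate of 35 % developing diabetes in placebo group in China".
- Error rate: "a type I error of 0.05 with two-sided".
- Result: "we have 80 % power to detect a 14 % difference in probiotics group at 2 year follow-up", which the section ties to the primary outcome.
- Dropout: "Considering a dropout rate of 10 %, the sample size for enrolled patients will rise up to 220 for all patients".

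The Randomization section fixes equal arms: "Participants are individually randomized to placebo or probiotics groups in a 1:1 allocation". The Statistical methods section names the primary test: "The difference between the groups in the incidence of diabetes is tested by means of the two-sided log-rank test". The Methods/Design part of the abstract gives the size before any dropout allowance: "The target sample size for intervention is 200 middle-aged men and women".

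**The concern.** Power follows from the sample size, the two event rates and the error rate. All of these are printed, so the 80% can be checked directly, and it looked far too high for 100 per arm and a 14-point difference from 35%.

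The figure carries the case for the trial's size. The Discussion relies on the sample size to support conclusions about efficacy and expects a significant reduction in diabetes. If true power is nearer 60%, the chance of missing the planned effect is about 40%, twice what is claimed. A non-significant result could then be read as having tested a 14-point benefit with 80% power when it had not.

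**Working it through.** **Inputs, all from the protocol article.** n = 100 per arm, p₁ = 0.35, two-sided α = 0.05 (z = 1.960), 80% power (z = 0.8416), 1:1 allocation, log-rank test, glucose tolerance tests at months 6, 12, 18 and 24. The 14% is read as an absolute difference, so p₂ = 0.35 − 0.14 = 0.21. The mean rate is 0.28.

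**1. Attempt to reproduce the 80% with the two-proportion test (pooled variance).**

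- Standard error under the null: √(2 × 0.28 × 0.72 / 100) = 0.06350
- Standard error under the alternative: √((0.35 × 0.65 + 0.21 × 0.79) / 100) = 0.06272
- Power = Φ[(0.14 − 1.960 × 0.06350) / 0.06272] = Φ(0.248) = **59.8%**

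Other versions of this comparison: unpooled 60.7%, arcsine 60.3%, exact enumeration of the chi-square test 60.1%, continuity-corrected 53.5%.

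**2. The planned log-rank test.**

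- Hazard ratio under proportional hazards: ln(0.79) / ln(0.65) = 0.547, so |ln HR| = 0.603
- Expected events with full follow-up: 100 × (0.35 + 0.21) = 56
- Schoenfeld power = Φ[(√56 / 2) × 0.603 − 1.960] = Φ(0.296) = **61.6%**
- Freedman formula: 59.1%
- Simulated log-rank test with assessments at the four planned visits and no loss: **about 60%**

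**3. Other readings that might give 80%.**

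| Reading | Power |
|---|---|
| All 220 enrolled analysed, 110 per arm, full follow-up | 63.9% (proportions), 65.8% (Schoenfeld) |
| One-sided 0.05, 100 per arm | 71.5% (proportions), 73.0% (Schoenfeld) |
| One-sided 0.05, 110 per arm | 75.0% (proportions), 76.5% (Schoenfeld) |
| 14% is the probiotics-arm rate (35% vs 14%), 100 per arm | 94% |
| 14% is a relative reduction (35% vs 30.1%), 100 per arm | 11% |

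The one-sided rows also contradict the stated two-sided test. None of these gives 80%.

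**4. What 80% would require.**

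- Per arm for 14 points: (1.960 × √(2 × 0.28 × 0.72) + 0.8416 × √(0.35 × 0.65 + 0.21 × 0.79))² / 0.14² = 160.3, so 161 (160 gives 79.9%)
- Events (Schoenfeld): 4 × (1.960 + 0.8416)² / 0.603² = 86.4, so 87, against 56 expected
- Difference detectable with 100 per arm: 17.3 points (35% vs 17.7%, close to a 50% relative reduction) by proportions, 16.9 points by Schoenfeld

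**5. Dropout allowance.** The protocol's 220 equals 200 × 1.10. To keep 200 after losing 10%, the figure is 200 / 0.90 = 222.2, so 223. Enrolling 220 leaves 220 × 0.90 = 198. At 99 per arm the two-proportion power is 59.4%, a loss of 0.4 points.

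**The case against.** The central arithmetic cannot be defended. The article is condensed and an analysis plan may exist, but every input is printed here, and a fuller document could reach 80% only by changing one of them.

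The fair objections concern what surrounds the main figure:

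- **Dropout.** The shortfall is two or three people. A log-rank test also uses a participant's follow-up until censoring, so the 198 completers are not the analysis set. Simulating 220 enrolled with 10% lost over 24 months gives about 62%, slightly more than 200 with no loss. This stands: the dropout step is a minor correction.
- **The abstract's 200.** It matches the target of 100 per arm before the allowance, so it is incomplete but not contradictory. This stands.
- **Precision.** The 61.6% assumes continuous-time proportional hazards, while six-monthly assessment gives about 60%. This stands: the text should say about 60% for either test.
- **Consequence.** The plan reports differences with 95% confidence intervals, which would show the imprecision of a null result. That softens the risk of over-reading it, but does not make the power statement correct.

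**Conclusion.** The power statement is wrong as written. The protocol's own inputs give about 60% (59–62% across the uncorrected two-sided methods), some 20 points below the stated 80%. Crediting the 220 enrolled raises it to about 62% with 10% loss, and to 64–66% at most with no loss.

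This rests on reading 14% as an absolute reduction, which is the natural sense; the two alternatives give 94% and 11%. The log-rank figures also assume proportional hazards and the stated 2-year rates. The dropout arithmetic and the abstract's figure are tidying, and the conclusion does not depend on them.

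**What to change.** Replace the power sentence with wording such as:

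> With 100 evaluable participants per arm, the trial has about 60% power at a two-sided 5% level to detect a reduction in 2-year diabetes incidence from 35% to 21% (about 56 expected events). Power of 80% is reached for an absolute difference of about 17 points.

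If the printed inputs are not the ones actually used, state the intended ones and show that they give the claimed power.

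As minor corrections, set the enrolment figure to 200 / 0.90 = 223 (224 for equal arms), or keep 220 and say that it yields 198 completers. Let the abstract say whether its 200 is before or after the dropout allowance.

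The power correction is wording only and needs no added participants or change of test. The cost is that the stated power becomes less favourable. Keeping the 80% claim for 14 points would instead need 161 per arm: 322 evaluable, and 322 / 0.90 = 358 enrolled.
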